### **Funding Sources: New Investigator Fund - Hamilton Health Sciences**

## BACKGROUND

The global population is living longer and the number of individuals 65 years and older is estimated to reach 2 billion by 2050 (1). A profound implication of the older adult population is the growing number of individuals that present with frailty. Frailty is a multidimensional syndrome characterized by a decline in function across multiple physiological systems including the cardiovascular, musculoskeletal, neurological, and immunological systems (2,3). When exposed to a stressor (e.g., fall, fracture, urinary tract infection), individuals who are frail are more vulnerable to experience a larger and faster deterioration in their health, which may manifest as functional dependency and the inability to return to baseline function and homeostasis (2). Frailty is an important risk factor for negative health outcomes such as increased falls (6,7), fractures (8), hospitalization (8), disability (8), nursing home admission (9), social isolation (4,10), and mortality (11). Frailty is more common in females than in males but mortality rates due to frailty are higher in males, and its prevalence is influenced by socioeconomic factors (12). It is estimated that approximately 1 in 6 community-dwelling older adults may have frailty and it gets worse with age, with 1 in 2 individuals 85 years and older being frail (13).

Older adults who are frail are more likely to be sedentary (14,15). Sedentary behaviour is defined as any waking behaviour in a standing, seating, or reclining posture, with a low energy expenditure ( $\leq 1.5$  metabolic equivalent of task [METs]) (16). The coexistence of frailty and sedentary behaviour worsens overall health (15). Sedentary behaviour is not merely the absence of moderate or vigorous physical activity but also a reduction in sit-to-stand transitions, stand time, and light physical activity (17). Most older adults who are frail spend more than 60% of their awake time in a seated position, which is equivalent to more than 9.5 hours/day of continuous sedentary behaviour (17). The deleterious health effects of sedentary behaviour are different to

those of physical inactivity and are partially independent of an individual's physical activity levels (17). Even older adults who meet the recommended aerobic exercise guidelines of moderate to vigorous physical activity might experience adverse effects of sedentary behaviour (17). Thus, interventions to reduce periods of prolonged sedentary behaviour are necessary.

Older adults who are frail are potentially the population that might benefit the most from a reduction in sedentary time as they are the most sedentary group and have the highest chronic disease burden (18). However, there is a dearth of evidence on effective interventions to reduce sedentary behaviour or total sedentary time in older adults, especially among individuals that are frail (15,19,21). Previous studies focused on reducing total sedentary time, while other studies aimed to increase physical activity levels with the assumption that sedentary time will be reallocated to physical activity (21). But, to date, such interventions have not been effective at reducing total sedentary behaviour time in older adults (15). Previous studies to reduce sedentary time and behaviour in older adults may not be effective because there is no research on the context of sedentary behaviour, about when and where to intervene, and which specific sedentary behaviours should be targeted (15,19). Almost all studies in older adults have assessed total sedentary time, which does not provide enough information to understand the context of sedentary behaviours (15,19). The main reason to understand context is because not all sedentary behaviours should be modified as some cognitively engaging sedentary behaviours (e.g., reading, socializing) appear to benefit health, while time spent in more passive activities may be detrimental. Therefore, the goal should not be to reduce total sedentary time, but rather identify sedentary behaviours that may be detrimental to the health of older adults who are frail (21).

### **3.0 Objectives and Aims**

Before we can develop an intervention to reduce sedentary behaviour among older adults, we must first assess the context of sedentary behaviour. Context is defined as the purpose of the sedentary behaviours, the location where the behaviours occur, the posture of the behaviours (e.g., lying, sitting), social context (e.g., alone or with others), and time of day the behaviours occur. The primary purpose of this study was to assess the feasibility of measuring the context of sedentary behaviour among older adults who are frail. We defined feasibility using recruitment, retention, and refusal rates (process) and the feasibility resource (i.e., can the tools capture context and are participants willing to use the tools). Our criteria for success were to recruit 20 participants within two months, 85% retention, and 20% refusal. Our secondary objectives are: 1) to determine the context of using objective and subjective measures to assess sedentary behaviours among older adults who are frail; 2) to identify which types of sedentary behaviours can be modified and when and where to intervene; and 3) to conduct an exploratory analysis to determine the association of certain types of sedentary behaviours on health-related outcomes. Context is defined as the *purpose* of the sedentary behaviours, the *location* where the behaviours occur, *posture* of the behaviours (e.g., lying, sitting), *social context* (e.g., alone or with others), and *time of day* the behaviours occur.

## METHODS

### Study Design

We will conduct a one-year mixed-methods longitudinal study with 20 older adults who are frail. To map the context of sedentary behaviour we will use objective (i.e., accelerometers and indoor positioning systems), and self-report (i.e., diaries) measures; we chose three measures as one measure alone does not provide enough information about context. Participants will be equipped with the accelerometer and indoor positioning system, and complete a diary of daily activities over three days (two weekdays and one weekend) in the winter and spring as sedentary

behaviour may differ by the season. We will also hold focus groups with participants to review the feasibility of using the indoor positioning system and diary and to review the results of the accelerometers, indoor positioning systems, and diaries to identify modifiable sedentary behaviours, and when and where to intervene.

## Study Setting

We will collect outcomes at St. Peter's Hospital or in a private clinic in Toronto, Ontario. Data from the accelerometers and indoor positioning systems will be collected remotely from the participant's home and stored on a secure Hamilton Health Sciences and McMaster University server.

## Participants & Recruitment

We aim to recruit 20 participants (65 years and older) living with frailty. We will recruit males and females as we anticipate that gender may influence sedentary behaviour through socially constructed norms and roles and can be affected by differential access to resources, opportunities, and power. We are collaborating with geriatricians at Hamilton Health Sciences and in Toronto to recruit participants. The physician will inform eligible participants of our study and provide participants a number to contact the research assistant. The research assistant will speak with interested participants to confirm eligibility and enroll them in the study.

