## Outcomes

### *Primary outcome*

The primary purpose of this study was to assess the feasibility of measuring the context of sedentary behaviour among older adults who are frail. We defined feasibility using recruitment, retention, and refusal rates (process) and the feasibility resource (i.e., can the tools capture context and are participants willing to use the tools).

Accelerometer: We will use the activPAL4™ accelerometer to collect data on posture and time of day over three consecutive days in the winter and spring. The activPAL4™ is a valid accelerometer in older adults that generates totals for the time spent lying, sitting, standing, and stepping every second of the day (22). The accelerometer is secured to participant's lower thigh with a 3M Tegaderm Transparent bandage and can hold its charge for up to 14 consecutive days. The accelerometer will not interfere with participants daily lives and can be used in the shower or pool. Data is collected wirelessly and stored on the hard drive of the accelerometer and will be transferred to a secured McMaster cloud by a research assistant.

Indoor Positioning System: We will use a McMaster developed indoor positioning system to obtain room/area level positioning information over three days in the winter and spring. The system is designed and validated to be used by older adults in their own homes without the need for a floor plan and only minimal initial setup and calibration (23). The participants will wear a commercially available, off-the-shelf smartwatch with customized software and plug-n-play ambient (nonwearable) beacons in in different rooms of the participant's homes. The smartwatches are

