### **Statistical analysis**

#### ***Primary outcome analysis***

Demographic data, feasibility process, and feasibility resources will be reported using means and standard deviations or as a count and percentage. Descriptive analyses were performed using Microsoft Excel (version 16.71). Missing values will be reported as missing. Individuals who were loss to follow-up can be included in the analysis if their data is available. Adverse events will be reported using narrative description.

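### The refusal criterion (20%) can be computed only over patients who telephone, because no count of eligible patients informed by physicians is described

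*Protocol*

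**What the plan says.** The Objectives and Aims section of the protocol sets three numeric targets: "Our criteria for success were to recruit 20 participants within two months, 85% retention, and 20% refusal". The Primary outcome section makes refusal part of the main result: "We defined feasibility using recruitment, retention, and refusal rates (process) and the feasibility resource".

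The Participants & Recruitment section describes how a patient reaches the study. It says that "We are collaborating with geriatricians at Hamilton Health Sciences and in Toronto to recruit participants", and then: "The physician will inform eligible participants of our study and provide participants a number to contact the research assistant". The next step is: "The research assistant will speak with interested participants to confirm eligibility and enroll them in the study".

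The Primary outcome analysis section gives only the form of the summary: "Demographic data, feasibility process, and feasibility resources will be reported using means and standard deviations or as a count and percentage". None of these sections states a numerator or denominator for refusal. The recruitment, data collection, trial management and data management sections do not describe a log of patients informed, a return of such a count to the study team, or any follow-up of patients who do not call.

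**The concern.** A refusal rate needs a count of people who were offered the study and said no. Here the offer is made in the physician's clinic, but the study team's knowledge begins with the patient's telephone call. Someone who hears about the study and decides against it need do nothing, and then leaves no trace in either numerator or denominator. The refusals that can be seen come from people interested enough to call.

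The Discussion presents this study as the first step towards designing an intervention. Uptake among frail older adults is therefore a figure that a later study would plan on. If the reported refusal rate describes callers but is read as describing all eligible patients approached, that planning starts from too favourable a number. The loss also cannot be repaired at analysis: an analysis plan can choose a denominator, but it cannot recover patients whom nobody counted.

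**Working it through.** The 20% threshold is asserted, not derived, so there is no calculation in the protocol to reproduce.

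**Inputs from the protocol.** Target enrolment E = 20; refusal criterion 20%, read as a ceiling.

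**Assumed inputs.** Eligible patients informed, N = 25 to 80; eligible callers, C = 22. The protocol gives neither number.

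**Step 1: what the ceiling allows.** With 20 enrolled and r refusals, the rate is r/(20 + r). Five refusals give 5/25 = 20.0% (met); six give 6/26 = 23.1% (failed).

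**Step 2: the two denominators.**

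- Refusal among eligible callers = (C − E)/C = 1 − E/C.
- Non-uptake among eligible patients informed = (N − E)/N = 1 − E/N.

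Since N is at least C, the first can never exceed the second. They agree only if every eligible patient informed calls.

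| Informed (assumed) | Eligible callers (assumed) | Enrolled | Refusal among callers | Non-uptake among informed |
|---|---|---|---|---|
| 25 | 22 | 20 | 2/22 = 9.1% | 5/25 = 20% |
| 30 | 22 | 20 | 9.1% | 10/30 = 33% |
| 40 | 22 | 20 | 9.1% | 20/40 = 50% |
| 60 | 22 | 20 | 9.1% | 40/60 = 67% |
| 80 | 22 | 20 | 9.1% | 60/80 = 75% |

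The caller rate stays the same however many patients were informed. Non-uptake is within 20% only if no more than 20/0.8 = 25 were informed.

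**Step 3: non-uptake is not the same as refusal.** Take 40 informed and 22 callers, which leaves 18 non-callers. If D of the 18 actually declined and the rest did not call for other reasons, refusal among those informed is (2 + D)/40:

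- D = 1: 3/40 = 7.5%, below the caller rate of 9.1%.
- D = 2: 4/40 = 10%, above it.
- D = 6: 8/40 = 20%, just meets the ceiling.
- D = 7: 9/40 = 22.5%, fails.
- D = 18: 20/40 = 50%.

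So the caller rate understates refusal in this example once two or more of the 18 non-callers have declined, and the criterion changes from met to failed at seven.

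**Step 4: chance of meeting the ceiling.** Suppose each person in the chosen denominator refuses independently with probability p. The chance of at most five refusals before the 20th enrolment is P(Bin(25, 1 − p) ≥ 20).

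| p (assumed) | Chance of meeting 20% or less |
|---|---|
| 0.05 | 0.9988 |
| 0.10 | 0.9666 |
| 0.15 | 0.8385 |
| 0.20 | 0.6167 |
| 0.30 | 0.1935 |
| 0.50 | 0.0020 |

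If callers are counted and 5 to 10% of them refuse, the criterion is met with probability 0.97 to above 0.99. If all informed patients are counted and 30 to 50% do not enrol, the probability is 0.19 down to 0.002. The choice of denominator can decide the result.

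**The case against.** The recruitment section says how patients arrive, not how contacts are logged. The referring geriatricians are collaborators, so a tally is fully compatible with the pathway. Denominators and screening logs for descriptive rates are often left to an analysis plan or to operating procedures. The trial management section mentions such procedures, and they are not shown. This is also a descriptive study of 20 people with no test on refusal, and the target of 20 recruits in two months gives a separate check on poor uptake.

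Part of this stands. A reader might infer that refusal cannot be measured under self-referral. The document does not support that: refusal among eligible callers is countable as written, and a clinic tally would supply the rest with the pathway unchanged. It is also fair that some non-callers may be ineligible, may have forgotten, or may have been informed after enrolment closed. Treating all of them as refusers would overstate refusal.

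The rest does not remove the problem. A choice of denominator can wait for an analysis plan, but collecting the count cannot, since it has to happen in the clinics while patients are being informed. The recruitment target measures speed, not proportion: 20 enrolments in two months could come from 25 patients informed or from 80.

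**Conclusion.** The point holds in a limited form. The primary feasibility outcome includes a refusal rate, and the procedures described yield that rate only over people who telephone. It can therefore understate refusal among all eligible patients informed. In the illustration, the same 20 enrolments give 9.1% among 22 callers and 50% non-uptake among 40 informed, on opposite sides of the criterion. Both 22 and 40 are assumptions. The direction of the error also assumes that more than a few non-callers did decline.

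A reader might go further and conclude that the criterion will be met almost automatically. The document does not show this. It would follow only if callers are the denominator and refuse at about 10% or less; at 20% the chance of meeting it is about 0.62, and a sixth refusal before the 20th enrolment fails it. If non-callers were counted as refusers, the criterion might well be missed.

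The absence of a direction on the 20% is a minor matter of wording: in a list of success criteria it can sensibly be read only as a ceiling.

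**What to change.** Add the following to the recruitment section before recruitment begins.

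1. Each referring clinic keeps a de-identified tally of patients informed of the study, closed when enrolment closes, and returns the count to the study team.
2. Define non-uptake = (informed − known ineligible − enrolled) / (informed − known ineligible). Patients found ineligible must leave both numerator and denominator. For example, with 40 informed, 10 found ineligible and 20 enrolled, this gives (40 − 10 − 20)/(40 − 10) = 10/30 = 33%. Removing the 10 from the denominator alone would give 20/30 = 67% and count ineligible people as refusers.
3. Report three counts separately: did not call, called and declined, called and found ineligible. Not calling is not always refusal, and the separate counts let the reader see how much depends on that.
4. State in advance which rate, non-uptake among those informed or refusal among eligible callers, is judged against the criterion, and word the criterion as no more than 20%.

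The cost is a small clerical task for the clinics and a few sentences of protocol text. The reported figure will probably look less favourable than a rate over callers. Eligibility of non-callers will remain unconfirmed, so non-uptake should be presented with that caveat.

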**Table 1: Inclusion and exclusion criteria**

| Inclusion criteria                                                                                                                                                                                                                              | Exclusion criteria                                                                                                                                                                                                                                                     |
|-------------------------------------------------------------------------------------------------------------------------------------------------------------------------------------------------------------------------------------------------|------------------------------------------------------------------------------------------------------------------------------------------------------------------------------------------------------------------------------------------------------------------------|
| 

1. 60 years and older;

2. Categorizes as frail on the FRAIL scale <math>\geq 3</math> of 5;

3. Lives in the Hamilton, Ontario and is a patient at the Hamilton Health Sciences;

 | 

1. Requires a wheelchair at least 55% of the awake day; needs to sit for long periods of time due to a medical condition; or not independently mobile (i.e., requires assistance from another individual to ambulate);

 |

|                                                    |                                                                                                                                             |
|----------------------------------------------------|---------------------------------------------------------------------------------------------------------------------------------------------|
| 4. Speaks English or can attend with a translator. | 2. Has travel plans or other commitments that means missing >30% of the rollout study period;
3. Unable to follow two-step instructions. |
|----------------------------------------------------|---------------------------------------------------------------------------------------------------------------------------------------------|

## Outcomes

### *Primary outcome*

The primary purpose of this study was to assess the feasibility of measuring the context of sedentary behaviour among older adults who are frail. We defined feasibility using recruitment, retention, and refusal rates (process) and the feasibility resource (i.e., can the tools capture context and are participants willing to use the tools).

Accelerometer: We will use the activPAL4™ accelerometer to collect data on posture and time of day over three consecutive days in the winter and spring. The activPAL4™ is a valid accelerometer in older adults that generates totals for the time spent lying, sitting, standing, and stepping every second of the day (22). The accelerometer is secured to participant's lower thigh with a 3M Tegaderm Transparent bandage and can hold its charge for up to 14 consecutive days. The accelerometer will not interfere with participants daily lives and can be used in the shower or pool. Data is collected wirelessly and stored on the hard drive of the accelerometer and will be transferred to a secured McMaster cloud by a research assistant.

Indoor Positioning System: We will use a McMaster developed indoor positioning system to obtain room/area level positioning information over three days in the winter and spring. The system is designed and validated to be used by older adults in their own homes without the need for a floor plan and only minimal initial setup and calibration (23). The participants will wear a commercially available, off-the-shelf smartwatch with customized software and plug-n-play ambient (nonwearable) beacons in in different rooms of the participant's homes. The smartwatches are

waterproof and can be used in the shower and pool. A typical setting will include one to two watches (depending on participants per household) and three to five Bluetooth beacons per participant. The Bluetooth beacons are labeled with the room's location and plugged into the wall socket (23). The system will detect and track the room-to-room movements of the participants at seconds to minutes intervals (23). Besides location, the system can also measure step counts, heart rate, blood oxygenation, and ambient conditions (lighting, temperature, humidity) (23). The indoor positioning system can be used in homes with multiple stories with multiple residents. The data is collected wirelessly and automatically stored on a secured McMaster cloud. The data can be analyzed through post processing or real-time for acute responses (e.g., falls) (23).

Diary: Each participant will be given an electronic or hard copy of a diary to complete over three days (two weekdays and one weekend during the winter and spring. The diary will ask participants to identify the purpose of the behaviour, the time of day, and social context. To improve diary adherence, we will have a research assistant call the participant the next day to record their 24-hour daily activity using the diary. There is good evidence that reminders improve adherence compared to no reminders (24).

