**Table 3: Data collection for Winter 2023 season**

| Time  | Data collection and timeline                                                                                                                                                                                                                                                    |
|--------------|----------------------------------------------------------------------------------------------------------------------------------------------------------------------------------------------------------------------------------------------------------------------------------------|
| Week 1       | Research assistant meets 5 participants (cohort 1) to equip the activPAL4™ and indoor positioning system watch to each participant and ensure it works properly. Participants will also receive their diary and complete several questionnaires (e.g., fall history, cognitive status) |
| Week 2       | Research assistant meets with the 5 participants from week 1 to collect the equipment and diary. The assistant will transfer the data from the activPAL4™ to a computer, and clean and charge the devices.                                                                             |
| Weeks 3 to 8 | Weeks 1 and 2 are repeated with a new group of 5 participants, until data are collected from 20 participants.                                                                                                                                                                          |
| Week 10      | Lead investigator holds a focus group with participants.                                                                                                                                                                                                                               |

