### *Data Entry*

Data will be entered and managed electronically on an editable PDF, which will be password protected and kept on a secure network system. The MoCA will be completed by the participant using a paper copy and stored at St. Peter's Hospital in a locked cabinet in a locked room that only the lead investigator and research assistant can access. The research assistant will be responsible for entering diary information and secondary outcomes into the editable PDF.

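### The next-day diary call is presented as a reminder but reads as assisted recall, so diary completeness alone cannot show whether participants were willing to use the diary themselves

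*Protocol*

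**What the plan says.** The protocol's primary outcome has a process part (recruitment, retention, refusal) and a resource part. The resource part asks "can the tools capture context and are participants willing to use the tools". The diary is one of three tools, alongside the accelerometer and the indoor positioning system.

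Under Primary outcome, the Diary paragraph starts from participant completion: "Each participant will be given an electronic or hard copy of a diary to complete over three days". It then says "we will have a research assistant call the participant the next day to record their 24-hour daily activity using the diary". The stated aim of the call is better adherence, and the support offered is "There is good evidence that reminders improve adherence compared to no reminders (24" (the quote breaks off at the reference number).

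Three other places bear on the point:

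- Table 3, Week 2: "Research assistant meets with the 5 participants from week 1 to collect the equipment and diary".
- Data Entry: "The research assistant will be responsible for entering diary information and secondary outcomes into the editable PDF".
- Primary outcome analysis: "Demographic data, feasibility process, and feasibility resources will be reported using means and standard deviations or as a count and percentage".

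None of these distinguishes entries by who made them, or by whether they were made before or during the call.

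**The concern.** A reminder prompts someone to do a task. The call described here comes after the day is over and, on its plain reading, does the task with or for the participant. Someone who never opened the diary but answered the telephone could end with a complete one.

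A completion percentage would then mix two things: the participant's own use of the diary, and acceptance of a daily telephone interview. The second is worth knowing, but it does not answer whether participants are willing to use the diary.

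The diary matters to the mapping. In Table 4 it is the only source for purpose and for social context, which are two of the four coded elements in every behaviour sequence (posture, environment, purpose, social context). A reader of the results would want to know whether those two elements came from a self-kept diary or from next-day interviews.

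**Working it through.** The protocol states no figure for diary completion, so there is none to reproduce. The check is a reading of the text, with a count for scale and a labelled illustration.

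**1. Number of diary-days.** Inputs: 20 participants (Study Design), three diary days per season, two seasons (Primary outcome, Diary). 20 x 3 x 2 = 120 planned diary-days. This is a maximum, because withdrawals would reduce it. As written, the call applies to all of them.

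**2. What a completion count identifies.** Suppose all 120 diary-days are complete and no source is recorded. The number completed by participants themselves can be anything from 0 to 120, that is, 0% to 100%. The count alone does not narrow this range.

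**3. Illustration (assumed values, none from the protocol).** Let s be the share of diary-days the participant completes unprompted, and c the share of the remaining days that the call fills. Observed completeness = s + (1 - s) x c.

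| s (assumed) | c = 0 | c = 0.9 | c = 1 |
|---|---|---|---|
| 0.5 | 0.50 | 0.5 + 0.5 x 0.9 = 0.95 | 1.00 |
| 0.8 | 0.80 | 0.8 + 0.2 x 0.9 = 0.98 | 1.00 |

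At c = 0.9, two levels of own use that differ by 30 percentage points (50% and 80%) appear as 95% and 98%, a difference of 3 points. If people who leave the diary blank also tend to miss the call, c is lower and the masking is weaker. At c = 0 there is none.

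**4. Whether the source can be recovered elsewhere.**

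- *Returned diaries (Table 3, Week 2).* If the assistant writes on a separate copy, the participant's returned copy may show some self-made entries. The protocol does not say which copy the assistant uses. A returned copy also would not show whether an entry was made before or after the call.
- *Data Entry.* The assistant's entry of diary information may be plain transcription. It neither shows that the assistant authored entries nor preserves their source.
- *Focus groups.* They ask users about the diary directly, so they inform willingness. Under Table 3 the winter group meets in Week 10, while the first cohort is equipped in Week 1, nine weeks earlier. They cannot reconstruct who made which entry.
- *Analysis plan.* Who made an entry, and when, is known only at collection. A later plan cannot create it.

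**The case against.** The strongest reply is that the call is part of the specified diary procedure. The objective concerns whether context can be measured, and nowhere demands unaided completion. On that view, data gathered with the call show whether the procedure yields purpose and social context. This stands for the capture half of the question. It does not settle the willingness half, because answering a call is not the same as using the diary, and the protocol hands the diary to participants to complete.

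A second reply is that the sentence about the call is loose and may mean only that the assistant prompts the participant to write. That reading is possible, and it is a reason to clarify the text. Even then, entries made before and after the prompt would need to be told apart.

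A third is that source flags belong on the diary form or in the outcome operating procedures mentioned under Trial Management and Staff Training, which are not shown. If they already carry such a flag, one sentence in the protocol closes the point.

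Three stronger readings might be inferred, and the document does not support them:

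- *That a success criterion is biased.* The criteria read "Our criteria for success were to recruit 20 participants within two months, 85% retention, and 20% refusal", and none uses diary completion. No pass or fail decision is affected.
- *That a later study will adopt an unaided diary on the strength of this result.* The Discussion speaks only of informing the co-design of an intervention.
- *That the primary question becomes unanswerable.* Call-assisted data and the focus groups both still contribute to it.

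**Conclusion.** The point holds in a limited form. As written, the call is assisted recall justified as a reminder, and diary completeness over at most 120 diary-days cannot by itself show participants' willingness to use the diary. Without a source flag, a complete set of diaries leaves the self-completed share anywhere between 0% and 100%.

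The 95% and 98% figures only illustrate how strong the masking could be under assumed inputs; they are not estimates for this study. The conclusion rests on two assumptions: that the call is carried out as the sentence reads, and that no form or procedure outside the protocol already records the source of entries.

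What is weakened is one component of a descriptive primary outcome, for one of three tools. It is worth correcting because the correction is cheap and cannot be made once the diaries have been collected.

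**What to change.** Keep the call and all the data it yields. State in the Diary paragraph whether it is a reminder or assisted recall, and add the following:

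1. At the start of each call, before any prompting, the assistant logs what the participant has already filled in.
2. Each entry, or at least each diary-day, is flagged as self-completed or recorded on the call, and the flag is carried into the study PDF.
3. Both shares are reported under feasibility resources, and the willingness result for the diary is based on the self-completed share.
4. All entries, whatever their source, are used for the context mapping.
5. If most entries come from calls, the tool is described in the report as a diary with next-day assisted recall.

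The cost is one extra field on the form, a moment per call and one more descriptive percentage. The diary figure may look less favourable. The flag has to be in use from the first diary-day.
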